## Abstract

**Background:**

The prevalence of type 2 diabetes mellitus (T2DM) and cardiovascular diseases (CVD) is rising globally. T2DM is particularly problematic in South Asia with an estimated 10–15% of Sri Lankans diagnosed with the disease. Exercise is known to improve blood glucose, lipid profiles, blood pressure and adiposity, key goals in the management of T2DM. However, much of the evidence to date has been gained from white Caucasians who have a different body composition and disease profile compared to South Asians. Similarly, the recreational exercise culture is new to Sri Lankans and the effects of exercise on T2DM has not been studied in this population.

**Methods:**

The Sri Lanka Diabetes Aerobic and Resistance Training (SL-DART) Study will be comprised of 2 components. Component 1 is a 12-week randomized controlled trial (RCT) to compare the effects of a supervised progressive resistance exercise program (RT) and aerobic exercise program (AT) with standard treatment/control (CN). Sedentary Sri Lankan adults with T2DM (aged 35–65 years) and with no contraindications to exercise will be randomized into one of 3 groups (AT, RT, CN). Exercise sessions will be conducted 2 days/week for 3 months. Baseline and post-intervention biochemical (glycemic control, lipid and liver profiles, inflammatory markers), anthropometric (height, weight, body circumferences), body composition, physical fitness, food preference (liking and wanting food) and quality of life parameters will be measured and compared between groups. Component 2 will be a qualitative study conducted immediately post-intervention via in-depth interviews to assess the barriers and facilitators for adherence to each exercise program.

**Discussion:**

SL-DART Study represents one of the first adequately powered methodologically sound RCTs conducted in South Asia to assess the effects of resistance and aerobic exercise in participants with T2DM. Triangulation of quantitative and qualitative outcomes will enable the design of a culturally appropriate therapeutic physical activity intervention for Sri Lankans with T2DM, and the initiation of a professionally driven and specialized clinical exercise prescription service.

**Trial registration:**

Sri Lanka Clinical Trials Registry; SLCTR/2016/017. Date registered 17.06.2016. Universal trial number U1111–1181-7561.

## Background

Type 2 diabetes mellitus (T2DM) and cardiovascular diseases (CVD) are major contributors to rising global mortality [1–3]. South Asia is home to almost one-fifth of the world’s population [4], a sub-population more prone to T2DM compared to other ethnicities [5]. In addition, an estimated 25 million people of South Asian origin (India, Pakistan, Bangladesh, Nepal, and Sri Lanka) [4] are living outside the region and similar prevalence rates have been reported in migrants in the USA, Canada, and various European countries [5]. There is a high prevalence of T2DM (10–15%) in South Asian Sri Lankans [6] who are at a greater risk of CVD [7] and develop T2DM at a younger age with increased incidence of complications (retinopathy, nephropathy, and coronary artery and cerebrovascular disease) than white Caucasians [5].

A number of explanations have been proposed to explain these ethnic differences, most commonly differences in body composition. For example, compared to white Caucasians, South Asians have increased abdominal adiposity/central obesity leading to insulin resistance (IR), T2DM and CVD [5]. This phenomenon can be explained in ‘adipose tissue compartment overflow hypothesis’ [8], stating the superficial subcutaneous tissue is less developed in South Asians, resulting in early expansion of the visceral and deep subcutaneous compartments [5, 9]. In addition the ‘thrifty genotype hypothesis’ states some people (possibly South Asians) can possess genes facilitating increased fat storage during food abundance for survival during later famine [10].

Sri Lanka is also experiencing a socio-economic or nutrition transition, a change from a more active agricultural lifestyle to a more sedentary lifestyle due to industrialization and urbanization and resultant overweight and obesity [6]. Historically, structured recreational exercise has not been a part of the culture in Sri Lanka [11] and it is uncommon to see recreational exercise groups, gymnasia and professionally trained staff. Poor food choices are also contributing to less than desirable health outcomes. For example, only 3–5% of Sri Lankan adults consume the recommended 5 portions of fruits and vegetables per day and diets are characterized by higher portions of rice and less protein (mainly by rice and pulses), almost half that of US adults [12]. Prevention and management of an estimated 1–1.5 million people with pre-diabetes and diabetes is causing an escalating burden to the Sri Lankan economy and society. There is a need to develop effective management strategies to prevent a worsening of the problem.

Exercise is known to improve blood glucose, lipid profiles, blood pressure [13] and visceral adiposity [14], key goals of diabetes management, with food intake and quality of life also considered as important factors. Combined aerobic exercise training (AT) and resistance exercise training (RT) interventions have been widely utilized in white Caucasians populations [15]with benefits also reported for either exercise modality when used individually [16, 17]. It has been suggested that South Asians could benefit more from RT due to their relatively higher adiposity and lower lean body mass compared to Caucasians [18]. Currently, no Sri Lankan studies have documented and very few South Asian studies have compared the effects of AT plus RT on people with T2DM. Secondly, low compliance and adherence is a common drawback in exercise interventions with information on the qualitative factors associated with non-adherence to exercise often overlooked [19]. Finally, relatively few South Asian studies have addressed food intake and the effects of AT and RT on food preference [20].

### Aims of the study

The primary aim of the Sri Lanka Diabetes Aerobic and Resistance Training (SL-DART) Study is to investigate the effect of two exercise modalities in Sri Lankan adults (aged 35–65 years) diagnosed with T2DM. A 12-week randomized controlled trial (RCT) will compare AT, RT and usual care on the primary outcome measure, glycemic control (HbA1c). Secondary outcome measures include percentage body fat, blood lipid and liver profiles, inflammatory markers, muscle strength, cardiovascular endurance, blood pressure, quality of life attributes and food preferences. A secondary aim is the qualitative assessment of barriers/facilitators to compliance and adherence to different modes of exercise via in-depth interviews.

To the best of our knowledge, a study of this nature has not been conducted in Sri Lanka or in other parts of South Asia. In a culturally diverse setting like Sri Lanka, the development of a feasible exercise intervention for T2DM would therefore be very novel. The experiences of SL-DART Study will enable the development of a culturally acceptable clinical exercise physiology service to people with T2DM.

## Methods

### Study design

Pilot studyComponent 1: A 12-week RCT will study the effects of a supervised RT and AT program on behavioral, anthropometric, physical fitness, appetite and biochemical parameters in sedentary Sri Lankan adults with T2DM (aged 35–65 years) with no contraindications to exercise. Outcomes will be compared between exercise programs and a control group who receive standard care.Component 2: A qualitative study will be undertaken immediately after the intervention to assess the barriers and facilitators for adherence to each program (refer to Figs. 1 and 2).

**Fig. 1 Fig1:**
[figure not shown]
Research plan

**Fig. 2 Fig2:**
[figure not shown]
Flow chart of sampling, recruitment and progression of RCT/Study 1

### Settings and study population

The study will be conducted in the Faculty of Medicine, University of Colombo, Sri Lanka with training carried out at the University’s Strength Training Gymnasium. The study population will be recruited from patients attending the medical and diabetic clinics of the National Hospital Sri Lanka (NHSL) and private sector endocrine clinics in Colombo after prior approval from the consultant physician in-charge.

### Preliminary study/pilot study

A 4-week pilot study was conducted to pretest the main study design methodology. Nine (*N* = 9) participants were recruited into each group (*n* = 3, Male: Female AT 1:2, RT 1:2, CN 2:1) and all completed the intervention. Main outcome of the pilot study was the change in HbA1c.The baseline values for HbA1c (Mean, SD) were 8.0(1.4)/7.7 (1.7)/8.3%(1.7) and post intervention values were 7.8 (1.2)/ 7.4 (1.1)/ 8.2%(1.7) for AT, RT and CN respectively. Challenges were identified in the difficulty of recruitment, including excessive time taken. A trained pre-intern medical doctor was recruited for initial participant contact. Participant response and tolerance to the intervention helped determine the duration of the practice period (4 sessions) necessary to teach the technical skills. The feasibility of the exercise protocol was improved by confirming the frequency of participant attendance (2 sessions/week), initial intensity and progression of exercises, testing the safety and first aid protocols and specific time points for measuring intervention outcomes. Technical and logistical constraints associated with coordination between laboratories and institutions were identified and improved. For example, access to the gymnasium and the investigation laboratories was improved by providing free car parking and transport facilities when needed. The availability of the principal investigator and exercise administrators at all times resulted in increased retention of participants. Pre-testing of all questionnaires was also undertaken.

### Process evaluation

A number of strategies for documenting the implementation of the intervention were developed with the pilot study. Standard Operating Procedures (SOPs) were developed for participant recruitment, randomization, screening, conducting pre- and post-intervention measurements and implementation of the exercise intervention. Dose of exercise to be delivered and its progression, reach for the participants (logs of participant attendance, participant experience about the intervention) were included in the information booklet. The intervention fidelity was separately assessed. Before the start of the study, the methods by which they would be documented, who would be responsible for completing the documentation, and procedures for data entry and evaluation was decided and the investigators and exercise supervisors were trained accordingly.

### Eligibility criteria

Inclusion criteria of participants include:Non-cognitively impaired Sri Lankan males and females (non-pregnant and not planning to fall pregnant), aged 35–65 years, and diagnosed with T2DM within the last 10 years.Not participated in any exercise program within the previous 6 months.

Participants will be excluded if blood HbA1c levels < 6.5% or > 11.5%, on insulin or thiazolidinedione therapy/other than standard oral hypoglycemic agents, advanced diabetes induced end-stage organ damage and history of significant cardiovascular (ischemic heart disease etc.), respiratory (asthma, chronic obstructive pulmonary disease etc.), musculoskeletal diseases. To maintain accuracy, the patient informant data will be cross-checked with the patient health records in the clinic (e.g. HbA1c levels, duration of diabetes, drug history etc.) by the principal investigator who is an experienced medical doctor.

### Informed consent

Written informed consent will be obtained from all participants prior to their entry into the study.

### Sample size

Ninety (*n* = 90) participants will be recruited from a roll-in method and allocated to RT group (*n* = 30), AT group (*n* = 30), or CN group (*n* = 30). The sample size was calculated considering the expected change of glycosylated hemoglobin (HbA1c) (primary outcome) of the participants. HbA1c is the main parameter to check long-term glycemic control [14]. Previous studies have reported that structured AT or RT had statistically and clinically significant reduction of absolute HbA1c by about 0.6% [21, 22]. Sample size was calculated to have 80% power to detect a moderate 0.65-SD difference in HbA1c, with an alpha/α value of 0.05. Additional participants will be recruited until the required number is achieved (*n* = 38) per group to account for the estimated drop-out rate of 15–25%.

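### 30 per group matches the stated 80% power at 0.65 SD only for an undeclared one-sided test; two-sided power is about 70%, and 38 recruited does not cover 25% dropout

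*Protocol article*

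**What the plan says.** The Sample size section of the protocol article sets 30 participants in each of three groups (RT, AT, CN), 90 in all. It bases this on the expected change in HbA1c, the primary outcome. Earlier studies of structured AT or RT, it says, "had statistically and clinically significant reduction of absolute HbA1c by about 0.6" per cent. It continues: "Sample size was calculated to have 80% power to detect a moderate 0.65-SD difference in HbA1c", "with an alpha/α value of 0.05". It then adds that "Additional participants will be recruited until the required number is achieved", giving 38 "per group to account for the estimated drop-out rate of 15–25" per cent.

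The Data and statistical analysis section plans a repeated-measures linear mixed model with age and sex as covariates and a significance threshold of 0.05. Neither section states whether the test is one- or two-sided, which formula was used, or which SD the 0.65 refers to. The abstract says that the trial "represents one of the first adequately powered methodologically sound RCTs conducted in South Asia".

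**The concern.** An alpha of 0.05 given without qualification is normally read as two-sided. On that reading, 0.65 SD at 80% power needs more than 30 per group, and the number it does need, 38, appears in the protocol only as the recruitment figure that allows for dropout. Stated power and stated size then disagree.

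What is at stake is how a null result is read. If power is nearer 70% than 80%, a true difference of 0.65 SD between an exercise group and control would be missed about three times in ten. A reader who relies on the abstract's statement about power would take a non-significant result as stronger evidence of no effect than it is. Type I error and the effect estimates are not affected.

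**Working it through.** **Inputs** (Sample size section): standardised difference d = 0.65; power 80%, so z = 0.842; alpha 0.05, so z = 1.645 one-sided or 1.960 two-sided; 30 per group, equal allocation; dropout 15–25%; 38 per group recruited. The check is a simple two-group comparison of means, n per group = 2(z_alpha + z_power)² / d², confirmed with the exact (noncentral t) calculation.

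**Reproducing the protocol's figures: one-sided 0.05**
- n = 2(1.645 + 0.842)² / 0.65² = 29.3, so 30. The t-test gives 29.97, so 30, with 80.0% power.
- Inflation for 20% dropout, the middle of the stated range: 30 / 0.80 = 37.5, so 38.
- Both 30 and 38 are reproduced.

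**The conventional reading: two-sided 0.05**
- n = 2(1.960 + 0.842)² / 0.65² = 37.2, so 38. The t-test gives 38.1, so 39.
- Power with 30 per group: 71.1% (normal approximation), 69.7% (t-test).
- The 30 is not reproduced.

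**What 38 recruited per group delivers (t-test)**

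| Dropout | Completers per group | Two-sided power | One-sided power | Two-sided detectable difference at 80% power |
|---|---|---|---|---|
| 15% | 38 × 0.85 = 32.3 | 73.0% | 82.6% | 0.71 SD |
| 20% | 38 × 0.80 = 30.4 | 70.3% | 80.5% | 0.73 SD |
| 25% | 38 × 0.75 = 28.5 | 67.4% | 78.2% | 0.76 SD |

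**Does 38 cover the stated dropout range?** The largest dropout that leaves 30 completers is 1 − 30/38 = 21%. At 25%, 30 / 0.75 = 40 would have to be recruited. This shortfall does not depend on sidedness.

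**How much baseline adjustment would be needed.** If 0.65 refers to the SD of raw HbA1c, adjusting for baseline with pre-post correlation r multiplies the residual SD by √(1 − r²). Thirty completers per group then reach 80% two-sided power at r of about 0.45 (normal approximation) to 0.47 (t-test). No correlation is stated, so r is an assumption here.

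**The case against.** The strongest reply is that the stated figures agree with each other. A one-sided 0.05 test gives 30, and 20% dropout takes 30 to 38. Nothing in the protocol rules out a one-sided calculation, and the size is derived from the effect of structured exercise, for which a directional test against control is coherent. This stands. A reader might infer that the 80% is simply false, or that a required 38 was mistakenly spent on dropout. The documents do not show that, because the match between 38 and the two-sided requirement may be coincidence. What remains is that the direction is undeclared, that readers will take 0.05 as two-sided, and that 38 falls short at 25% dropout on either reading.

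A second reply is that the planned analysis is a mixed model rather than a t-test, and using the baseline values could recover the lost power. That is possible, but the sample size text claims no such gain and states no correlation.

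Two stronger readings are also tempting. One is that only 90 will be recruited and dropout then cuts into that number. The sentence on additional participants points the other way: 90 is most naturally the completer target and 38 × 3 = 114 the recruitment number, loosely worded. The other is that the pilot contradicts the effect size, because 0.6 / 0.65 implies an SD of 0.92 percentage points while the pilot SDs run from 1.1 to 1.7. Those are SDs of HbA1c at a single time, from three people per group. The protocol neither equates 0.6% with 0.65 SD nor says which SD it used. On change scores the two could agree if the pre-post correlation were about 0.82. The comparison illustrates why the SD should be named; it does not show an error.

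**Conclusion.** The point holds in a limited form. The stated power and size agree for a simple two-group comparison only if the test is one-sided at 0.05, which the protocol does not say. Under the conventional two-sided test, power at 0.65 SD is about 70% with 30 completers per group, and about 73% to 67% over the protocol's own dropout range from 38 recruited. Whichever test was meant, the recruitment number does not support 30 completers at the upper end of that range, although the one-sided loss is small (78% against 80%).

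These figures assume an unadjusted comparison of one exercise group with control at the full 0.05, with 0.65 expressed in the SD of the quantity analysed. A stated and justified baseline-adjustment gain could restore 80%.

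**What to change.** In the Sample size section:
- State whether the test is one- or two-sided, and name the SD to which 0.65 refers (raw HbA1c, change, or adjusted residual).
- Say plainly that 30 per group (90) is the completer target and 38 per group (114) the recruitment number, and that 38 covers dropout only to about 21%.
- If the test is two-sided, restate power as about 67–73% at 0.65 SD after 15–25% dropout, or the detectable difference as about 0.71–0.76 SD. Keep 80% only if a baseline-adjustment gain is stated with its assumed correlation. Qualify the abstract's claim of adequate power to match.
- If a one-sided calculation was used, say so, restrict it to exercise versus control, and give the two-sided power beside it.

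The cost is protocol wording and a less favourable stated power. The design does not have to change.

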### Randomization and blinding

Adaptive covariate randomization will be carried out to minimize allocation bias and balance important covariates among treatment groups, which has been recommended for clinical research with low sample sizes [23]. Staff who are responsible for exercise administering and data collection will be blinded for the randomization process. Blinding of exercise administers and participants to the intervention is not possible in exercise intervention trials, whereas the outcome assessors (trained staff in independent tertiary care laboratories) will be blinded [22]. Data analysis will be done by the first author on a de-identified database.

### Participant assessment and documentation

An information booklet will be used to record interviewer-administered data collected from participants. Initially, demographic data (name, age, gender, marital status, occupation and income level), screening data for eligibility, and background physical activity levels will be documented. During the study, pre- and post-intervention behavioral, appetite, anthropometry, physical fitness, biochemical parameters and the individual exercise protocols, plus details of each exercise session (24–30 sessions), will be documented by the exercise supervisors.

### Screening

Screening will be undertaken via a thorough medical history and physical activity readiness questionnaire (PAR-Q) [24] followed by a physical examination conducted by a qualified medical practitioner. The objective is to exclude any condition mentioned in the exclusion criteria and ensure safety for progressive exercise. Eligible participants will be allocated to one of the groups and complete a 2D Echocardiogram and Exercise/Stress electrocardiogram/ECG supervised by a consultant cardiologist. Patients who fail the test will be excluded from the study and referred for specialist care (see Fig. 2).

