### Intervention

The theoretical basis for the exercise intervention was gleaned from current literature and guidelines from the American College of Sports Medicine (ACSM) and American Diabetes Association (ADA) [25, 26]. Eligible participants will take part in an educational practice period (4 sessions) at the University of Colombo strength gymnasium 2 weeks prior to start of the intervention proper. These sessions will assist participant familiarization with the environment, teach them skills techniques, assess tolerance to the frequency and intensity of exercises etc. Participants will start with minimum tolerable intensity, duration/repetitions and slowly progress to the required exercise dose (AT: 60–70% of HR _max_ for 75 min, RT: 7 exercises all repetitions maintaining 50% repetition maximum (RM) using correct technique). Once participants achieve the minimum requirement, as assessed by the principal investigator, they will start the intervention proper. Pre-intervention (i.e., baseline) parameters will be measured one week before starting the intervention proper (see Fig. 3).

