#### Control group-active control

This group will be provided with standard care - attending normal clinic visits to a consultant physician prescribing medication and providing general health education. No specific instructions will be provided regarding exercise nor additional information regarding dietary modifications. The group will complete all pre- and post-intervention measurements and participants will be contacted via telephone once every 2 weeks during the 12-week period.

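### Participants are allocated before the echocardiogram and exercise ECG that decide whether they stay in the study, so eligibility exclusions fall after randomisation

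*Protocol article*

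**What the plan says.** The Screening section of the protocol article begins with medical history, PAR-Q and a physical examination. It then continues: "Eligible participants will be allocated to one of the groups and complete a 2D Echocardiogram and Exercise/Stress electrocardiogram/ECG supervised by a consultant cardiologist". The consequence of a failed test is stated directly: "Patients who fail the test will be excluded from the study and referred for specialist care".

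The Methods paragraph of the Abstract implies the reverse order. There, sedentary adults with T2DM and "with no contraindications to exercise will be randomized into one of 3 groups (AT, RT, CN".

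Two later sections bear on what happens between allocation and the start of training:

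- **Intervention** describes a four-session practice period with a target exercise dose given for AT and for RT, and adds: "Once participants achieve the minimum requirement, as assessed by the principal investigator, they will start the intervention proper". On timing it says: "Pre-intervention (i.e., baseline) parameters will be measured one week before starting the intervention proper".
- **Control group-active control** says of the control arm: "No specific instructions will be provided regarding exercise nor additional information regarding dietary modifications".

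Randomization and blinding specifies a covariate-adaptive allocation intended to balance important covariates. It says that outcome assessors in independent laboratories will be blinded and that participants and those who administer the exercise cannot be. Sample size gives 30 per group, raised to 38 for 15–25% drop-out.

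**The concern.** A test that decides whether someone belongs in the trial should be finished before the arm is assigned. When it comes afterwards, three things are at stake.

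1. **The comparison.** People removed from the study after allocation provide no outcome, so the groups analysed are not the groups randomised. If the arm is known when a borderline result is judged, the decision can lean one way for a person assigned to exercise and another way for a control.
2. **The balance.** Covariate-adaptive allocation balances the people allocated. Removing some of them afterwards undoes part of that balance. The age and sex terms in the mixed model (Data and statistical analysis) do not restore the randomised comparison.
3. **The numbers.** The allowance from 30 to 38 per group is described as covering drop-out. Exclusions at the cardiac test come on top of that unless they are replaced.

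The practice period raises a related, weaker issue. A condition for starting training can apply only to participants who train, and baseline is tied to that start. An exercise-arm participant who stalls at this step might have no baseline measured.

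**Working it through.** **Step 1: order of events.** Set side by side, the texts give two sequences.

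| Source | Sequence |
|---|---|
| Abstract, Methods | no contraindications → randomised |
| Screening | history, PAR-Q, examination → allocated → echocardiogram and exercise ECG → those who fail excluded from the study |

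Both cannot describe the same trial, because the cardiac test is part of establishing that there is no contraindication. Fig. 2, cited for this step, is not available here. Whatever it shows, the two texts need to be reconciled.

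**Step 2: is the exclusion tied to arm?** The Screening sentence covers all groups, so the test is not arm-specific. Blinding is promised for outcome assessors in independent laboratories. The supervising cardiologist is not named there, and no sentence says that the allocation is withheld when pass or fail is decided. Influence of the arm is therefore possible but not shown.

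**Step 3: the plan's own sample size.** Inputs from Sample size: difference 0.65 SD, 80% power, alpha 0.05 (sidedness not stated), three equal groups.

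n per group = 2 × ((z for alpha + z for power) / 0.65)²

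- One-sided: 2 × ((1.645 + 0.842) / 0.65)² = 29.3, rounded up to 30.
- Two-sided: 2 × ((1.960 + 0.842) / 0.65)² = 37.15, rounded up to 38.

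So the stated 30 reproduces as a one-sided figure, and 30 / (1 − 0.20) = 37.5, rounded up to 38, reproduces the recruitment target. The sidedness is a separate matter and this point does not rest on it.

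**Step 4: cost in numbers and power.** The article gives no cardiac failure rate, so e = 0–15% is an assumption. Over 3 × 38 = 114 allocated, 5–15% means about 6–17 people removed after allocation. Evaluable per group = 38 × (1 − e) × (1 − drop-out), with no replacement. Power is from a two-sided 0.05 t-test at 0.65 SD.

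| Assumed e | 15% drop-out: n, power | 25% drop-out: n, power |
|---|---|---|
| 0% | 32.3, 73% | 28.5, 67% |
| 5% | 30.7, 71% | 27.1, 65% |
| 10% | 29.1, 68% | 25.7, 63% |
| 15% | 27.5, 66% | 24.2, 60% |

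The first row shows that most of the gap to 80% exists with no cardiac failures at all. At e = 10% the loss due to this point is 73 − 68 = 5 points at 15% drop-out and 67 − 63 = 4 to 5 points at 25% (67.4 − 62.6 = 4.8).

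**Step 5: the practice-period step, as a what-if only.** Suppose a fraction f of an exercise arm were lost here and those lost differed by D SD in outcome from those kept. The mean of the retained arm would then shift by f × D: 0.05 × 0.5 = 0.025 SD, or 0.10 × 1 = 0.10 SD, the latter being 0.10 / 0.65 = 15% of the target difference. Both f and D are assumptions, and the article supports no particular value or sign.

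**The case against.** **The sequence may be loose wording.** One sentence under a Screening heading joins allocation and testing with a simple conjunction, the Abstract points the other way, and the figure is not shown. Actual conduct may therefore be sound. That limits certainty about conduct, but the text as written states the wrong order.

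**The test is uniform and carried out in an outside clinical setting.** This stands. A uniform exclusion on pre-existing cardiac status mainly costs numbers; bias needs a decision influenced by the arm. A reader might infer that the cardiac exclusions will differ by arm. The documents do not say that the cardiologist knows the allocation, so only the absence of stated concealment can be raised.

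**The practice period is not an exclusion.** This also stands. A reader might infer that slow achievers are removed, that only the less fit or less adherent are lost, and that this favours exercise. The Intervention section makes only the start of training conditional. It describes gradual progression and never says that anyone is dropped. That controls have no such step is itself inferred, from the targets given for AT and RT only and the lack of exercise instruction for controls.

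**Losses may be replaced.** Sample size speaks of recruiting additional participants until 38 per group is reached. If that covers cardiac failures, the power loss in the table largely disappears. Replacement does not make the exclusions pre-randomisation, however.

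**Analysis populations are often left to a fuller document.** Agreed, and the lack of such a definition here is not counted as a fault.

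**Conclusion.** The point holds for the order of events. Screening allocates participants before a test that determines whether they remain in the study, and removes those who fail. That creates exclusions after randomisation and contradicts the Abstract. Arm-related judgement at the test is an unguarded possibility, not a demonstrated bias.

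The size is modest on the figures available: about 5 points of power at an assumed 10% failure rate without replacement. A reader might attribute the whole shortfall to 63–68% to this point. That would be wrong, because 67–73% is reached with no cardiac failures. No bias estimate can be given, since the failure rate, any difference between arms and the outcomes of those removed are all unknown.

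The practice-period requirement is a secondary risk. If anyone were lost there, the loss would fall on AT and RT alone and might precede the baseline measurement. The article states no such loss.

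**What to change.** 1. Reword Screening so that every test that decides eligibility is completed and its result recorded before the allocation call. This includes the echocardiogram and exercise ECG already planned for all groups. Bring the Abstract and Fig. 2 into line.
2. State that every allocated participant has baseline measured, is followed up and is analysed in the allocated arm, including anyone in AT or RT who has not reached the practice-period requirement. Fix the baseline date so that it does not depend on passing that step.

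The first change adds no procedure and alters only the visit order, so allocation happens slightly later. The second brings a little more follow-up work for participants who are slow to start or do not start training. Neither changes any exercise dose or clinical criterion.
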